## Abstract

**Background:**

Older adults are at high risk for toxicity due to cancer treatment and increased risk for adverse events related to chemotherapy-induced nausea and vomiting (CINV). Unfortunately, older adults report multiple treatment-related symptoms but use few strategies to self-manage these symptoms due to erroneous beliefs related to the effectiveness of commonly taught self-management strategies. We developed a novel serious game, Managing at Home (MAH), to help older adults learn how to effectively self-manage CINV at home.

**Objective:**

This study has 2 aims. Aim 1 is to examine changes in CINV severity, self-management behaviors, functioning, quality of life, cognitive representation, and health care use within the intervention group from baseline (T_1_) to completion of the study (T_6_). Aim 2 is to determine the efficacy of the MAH intervention by comparing differences in primary outcomes (CINV severity and health care use) and secondary outcomes (self-management behaviors, functioning, and quality of life) between the intervention and control groups at each follow-up visit (T_2_-T_6_) and completion of the study (T_6_).

**Methods:**

This is a longitudinal randomized clinical trial. We will collect data from 500 older adults receiving cancer-related chemotherapy at baseline (T1) and at each treatment cycle until cycle 6 (T6). Participants will be enrolled if they are 60 years or older of age, are newly diagnosed with cancer, being treated with any chemotherapy agent with moderate or high emetic potential, are on a 2-, 3-, or 4-week treatment cycle, are proficient in English, and have a telephone. Previous diagnosis or treatment for cancer, end-stage disease with less than 6 months to live, and uncorrected visual or hearing impairment are exclusion criteria.

**Results:**

This study was funded in September 2022 and received institutional review board approval in October 2022. As of July 2023, the enrollment of participants is ongoing and currently has 130 enrolled participants. Data collection and analysis will be complete in 2027.

**Conclusions:**

This study addresses self-management of CINV in older adults using an innovative serious game. The MAH intervention uses simulation and gaming technology to engage older adults in active learning in order to reframe erroneous perceptions about symptom self-management. If shown to be effective, it can easily be adapted to include other cancer-related symptoms or other chronic illnesses.

**Trial Registration:**

ClinicalTrials.gov NCT05838638; https://clinicaltrials.gov/study/NCT05838638

**International Registered Report Identifier (IRRID):**

DERR1-10.2196/64673

## Introduction

### Background

Older adults (≥65 years) represent about 15% (46 million) of the US population, and the rate is expected to double (90 million) by 2050 [1-3]. They also represent 55% of all cancer diagnoses [2,4]. With an aging population, the number of older adults with cancer will also increase, taxing limited health care resources. Despite advances in antiemetic therapy, older adults diagnosed with cancer experience chemotherapy-induced nausea and vomiting (CINV) [5]. Although older adults are less likely to have CINV symptoms, they are more likely to experience serious consequences (eg, dehydration and renal impairment) than younger adults [6-8] due to the presence of multiple comorbidities, compromised organ function, frailty, and decreased overall functioning [9-11]. CINV occurs in up to 80% of adults receiving chemotherapy [12,13] and can lead to metabolic and nutritional issues (eg, loss of appetite, weight loss, and malnutrition), decrease in self-care and functioning, decline in physical and mental status, and poor quality of life (QOL) [12]. Up to 47% of adults receiving moderate to high emetogenic chemotherapy will experience a hospital admission (HA) related to CINV [14,15] and ~20% will have an unplanned emergency department (ED) visit [16]. The Centers for Medicare and Medicaid Services [17] urge improving care and reducing unplanned ED visits in those receiving cancer treatment. Therefore, interventions are needed to decrease CINV symptoms, improve functioning and QOL among older adults, and reduce health care use due to poor CINV symptom self-management.

Despite clinical guidelines for managing CINV, ~49% of adults with cancer are undertreated for CINV [13,18], and prevention of CINV remains a challenge [5]. Risk factors for undertreatment include the type of chemotherapy, being treated in the outpatient clinic, and out-of-pocket costs for antiemetics [18]. Health care practitioners report that managing breakthrough nausea within the first 5 days after chemotherapy is a common occurrence, while managing delayed CINV is the most challenging [19]. About 32% of practitioners report the need to stop or delay cancer treatment in patients due to CINV [19].

While the above risk factors for CINV are beyond the scope of this study and control of patients with cancer, there are many pharmacologic and nonpharmacologic strategies that older adults can use to prevent or self-manage CINV and minimize negative effects. Older adults diagnosed with cancer experience multiple side effects from chemotherapy treatment, yet do very little to manage those side effects [20,21]. In general, older adults modify their lives to reduce the severity of side effects rather than engaging in active self-management of those side effects [22-25]. Older adults are slower to take action against symptoms than younger adults [26], tend to minimize symptoms and their consequences [27-29], and normalize and interpret symptoms as part of aging, leading them to delay seeking or starting treatment [26,30]. They also delay treatment due to being uncertain about the symptom’s severity or seriousness and believing that treatment or management is not possible [28]. Some older adults believe that side effects have to be endured as part of their cancer treatment [31,32]. However, those who believe they can manage their symptoms engage in self-management strategies [33]. Interventions, such as the Managing at Home (MAH)-CINV [34], which specifically address older adults’ erroneous symptom beliefs and encourage them to engage in preventative and self-management behaviors may be able to alter their responses to side effects due to cancer treatment [35].

Printed standard patient education material for CINV based on well-known treatment and prevention guidelines (Textbox 1) are routinely provided to new patients and their family members so they can self-manage CINV at home. However, there is very little research related to how older adults self-manage side effects at home during chemotherapy treatment. Prior research by this team shows that without additional educational intervention, only ~25% of older adults who experience nausea actively manage it with medication [21]. Instead, they prefer to modify their activities or use dietary strategies to manage their nausea [21]. However, we found that with additional technology-based education and intervention and a change to their erroneous symptom beliefs, preventative and self-management strategies improve overall with twice as many older adults engaging in CINV prevention activities compared to a control group [34]. Results from our pilot study using the MAH educational intervention indicate that over 55% of participants used hydration as a strategy to prevent CINV [34]. Dietary strategies, taking antiemetics, and relaxation techniques were the top appropriate preventative and self-management strategies used by participants [34]. Although our educational intervention increased the use of these strategies, our sample size was too small to examine the effectiveness of the MAH intervention to improve the CINV symptoms*.* Therefore, the goal of this project is to examine the effectiveness of the MAH intervention in reducing CINV symptoms among older adults.

At the time that our team developed the MAH intervention, few studies used technology-based platforms to educate older adults. Those who used these platforms focused on Wii Fit games to promote exercise [36], mobile devices to increase physical activity [37], and avatars and touchscreen technology to manage diabetes [38]. However, since then, serious gaming interventions are becoming more popular. Serious gaming is a well-established method designed to support learning and change health-related behavior by engaging individuals in an entertaining experience [39-41]. Serious gaming capitalizes on fun while promoting behavior change [40]. It is also consistent with our goal of changing behavior by changing their beliefs about self-care related to CINV.

Recent research has used serious gaming among older adults to increase self-management knowledge about heart failure [42], detect cognitive impairment [43], provide cognitive task training [44], promote active lifestyle [45], provide education about pain management after surgery [46], detect frailty through grip strength [47], and provide training on how to avoid falls [48]. All of these studies have shown that serious gaming is usable, feasible, and acceptable for use in older adults. Our pilot study showed that it is feasible to recruit older adults diagnosed with cancer to participate in our intervention using serious gaming, and the MAH has high acceptability among users [34]. Coupled with the positive impact the MAH had on increasing preventative and self-management behaviors, this novel intervention shows promise in influencing how older adults think about CINV management and engage in self-management behaviors.

Older adults are using more technology on a day-to-day basis and becoming more proficient. A 2020 American Association of Retired Persons report states that older adults are embracing new technology, with over 50% purchasing some sort of technological product in the past year. Over half of the population aged 50 years and older own a smart tablet, and about 77% of older adults own a smartphone [49]. Another 2021 American Association of Retired Persons report states that older adults increased their use of technology during the recent COVID-19 pandemic and have bridged the “digital gap” between them and younger generations. Due to the pandemic and resulting social isolation, older adults, including people aged 70 years and older purchased, and used, more devices such as smartphones, tablets, and wearables [50]. This shows that older adults are embracing technology and are becoming more literate with the technology. This supports the use of our technology-based intervention and data collection strategies.

Common recommended chemotherapy-induced nausea and vomiting interventions.
**Pharmacologic**
MedicationAntiemetic therapy as prescribed by the physician
**Nonpharmacologic**
NutritionEat dry food, small meals, and bland and easy to digest foodsSit up after eatingAvoid cooking odorsAvoid spicy and greasy foodsHydrationDrink 8 to 12 cups of liquid per dayDrink even if not thirstyInclude liquids like soup, ice pops, flavored ices, and gelatinLimit caffeine productsComplementaryRelaxation, yoga, behavioral therapy (distraction and meditation), guided imagery, controlled breathing, environmental changes, and acupuncture or acupressure

### Aims and Hypotheses

The goal of this project is to examine the effectiveness of the MAH intervention in reducing CINV severity and health care use and increasing functioning and QOL. We aim to:

Aim 1: Examine changes in CINV severity, self-management behaviors, functioning, QOL, cognitive representation, and health care use within the intervention group (IG) from baseline (T_1_) to completion of the study (T_6_).We hypothesize that the IG will report lower levels of CINV severity and health care use and higher levels of self-management, functioning, cognitive change, and QOL from baseline to the completion of the study.Aim 2: Determine efficacy of the MAH intervention by comparing differences in primary outcomes (CINV severity and health care use) and secondary outcomes (self-management behaviors, functioning, and QOL) between the IG and control group at each follow-up visit (T_2_-T_6_) and completion of the study (T_6_).We hypothesize that the IG will report lower levels of CINV severity and health care use at T_2_-T_6_ than the control group.We hypothesize that the IG will report higher levels of self-management behaviors, functioning, and QOL at T_2_-T_6_ than the control group.

## Methods

### Study Design

Using a randomized clinical trial, we will enroll older adults from 2 clinical sites in Florida. Participants will be randomized to either the IG or attention control group (ACG). The IG will receive the MAH at baseline, and the ACG will receive it at the end of the study. Data will be collected over 6 months or 6 chemo cycles (T_2_-T_6_). Data related to CINV severity, self-management, functioning, QOL, and health care use at baseline and at the 6 time points will be collected from both groups.

### Settings

The intervention will be offered at outpatient treatment centers at a community cancer center in Orlando, Florida, and a Comprehensive Cancer Center in Miami, Florida, that provide care to over 6000 adults aged 60 years and older each year. These numbers indicate an ample sampling pool of older adults diagnosed with cancer.

### Study Participants

A sample of 500 participants will be enrolled if they meet the following inclusion criteria: ≥60 years of age, newly diagnosed with cancer, treatment with any chemotherapeutic agent of moderate or high emetic potential [51], on a 2-, 3- or 4-week treatment cycle, proficient in English, and have a telephone. Exclusion criteria are previous diagnosis or treatment for cancer, end-stage disease with less than 6 months to live, and visually or hearing impaired without corrective device. Dementia or cognitive impairment is not a concern with this population since they have already been cognitively screened to consent to treatment at each site. These criteria were also successfully used in our pilot study.

### Power Analysis and Sample Size

For aim 1, when the outcome of interest is continuous (eg, CINV severity and number of self-management behaviors), a sample of 100 participants, measured continuously throughout the study period between T1 and T6, achieves a power of 0.904 when using a chi-square test from a generalized estimating equation (GEE) analysis to test whether the average slope of the participants differs significantly at a significance level of .05. The residual SD is anticipated to be 1.00. Missing values are assumed to occur completely at random (missing completely at random [MCAR]). These missing value proportions will be combined to form the pairwise observant probabilities using the independent method. The anticipated proportions missing at each measurement time are 0.00, 0.08, 0.16, 0.24, 0.32, and 0.40. The first row of the autocorrelation matrix of the responses within a participant is assumed to be 1.0000, 0.4000, 0.1600, 0.0640, 0.0256, and 0.0102. Other rows follow the same pattern. For aim 1, a total of 254 participants, each scheduled to be measured 6 times, achieves a power of 0.90 when using a 2-sided Wald test from a GEE analysis with a count outcome (eg, QOL) to test whether a μ1(1) of 0.500 differs from a μ2(1) of 1.000 at a significance level of .05. μ1(0) and μ2(0) are assumed to be 1.000. Missing values are assumed to occur completely at random (MCAR). These missing value proportions will be combined to form the pairwise observant probabilities using the independent method. The anticipated proportions missing at each measurement time are 0.00, 0.08, 0.16, 0.24, 0.32, and 0.40. The first row of the autocorrelation matrix of the responses within a participant is assumed to be 1.000, 0.500, 0.250, 0.125, 0.063, and 0.031. Other rows follow the same pattern.

For aim 1, when the outcome of interest in binomial (eg, resource use), a sample of 357 participants, each scheduled to be measured 6 times, achieves a power of 0.90 when using a 2-sided Wald test from a GEE analysis with the binary outcome to test whether a P1(1) of 0.500 differs from a P2(1) of 0.250 at a significance level of .05. P1(0) and P2(0) are assumed to be 0.500. Missing value (MCARs) proportions will be combined to form the pairwise observant probabilities using the independent method. The anticipated proportions missing at each measurement time are 0.00, 0.08, 0.16, 0.24, 0.32, and 0.40. The first row of the autocorrelation matrix of the responses within a participant is assumed to be 1.000, 0.500, 0.250, 0.125, 0.063, and 0.031. Other rows follow the same pattern.

For aim 2, based on the assumption of a nausea severity mean score of 6.20, range from 2 to 9, an SD of 2.44, and a clinically meaningful difference in mean nausea severity score of 1 between the IG and control group, a sample size of 500 participants (250 per group), measured between 6 and up to 30 times (depending on the outcome variable of interest), achieves 87% power to detect a difference between the (fixed) group means. The ratio of the subject-specific slope variance to σ² is 0.100. The correlation between measurements within a participant is 0.100. The test was based on a mixed model regression analysis using a significance level of .05. This power analysis was calculated using PASS 20 (NCSS LLC). Anticipating an attrition rate of ~22%, we will seek to enroll 610 older adults for this study. Attrition to mortality is not expected to be high due to the exclusion criteria for those with less than 6 months to live.

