The effect of the intervention on primary and secondary outcomes at each follow-up visit and at the completion of the study will be assessed using generalized linear mixed models (GLMMs). GLMMs are an extension of general linear models allowing the study of within- and between-subjects repeated measures variations over time. GLMMs can also be used to fit normal and nonnormal response variables, as it is the case in this study. The interaction of time and treatment will be assessed by using an interaction term in the longitudinal models. All models will control for the effects of demographic and experiential variables listed in aim 1. The analysis will be 2-tailed and conducted with SAS (version 9.4).

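### The enrolment target is given as both 500 and 610, and 610 is the wrong inflation for 22% attrition: it leaves about 476, not the 500 behind the 87% power

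*Protocol article*

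**What the plan says.** Power Analysis and Sample Size bases the Aim 2 calculation on "a sample size of 500 participants (250 per group") and says that this number "achieves 87% power to detect a difference between the (fixed) group means". The same paragraph then adds: "Anticipating an attrition rate of ~22%, we will seek to enroll 610 older adults for this study".

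Other sections give a different number:

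- Study Participants: "A sample of 500 participants will be enrolled if they meet the following inclusion criteria".
- Abstract, Methods: "We will collect data from 500 older adults receiving cancer-related chemotherapy", with collection starting at baseline.
- Part 2 of the intervention (the self-care discussion) equates 10% of game players with n=25. That implies 250 people in the intervention group at game play, hence 500 randomised 1:1.

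No section explains how 500 and 610 relate.

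**The concern.** There are two separate faults.

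First, the power section and Study Participants both say how many people will be enrolled, and they give different numbers. The Results section reports 130 enrolled as of July 2023 with recruitment continuing, so the point at which recruitment should stop was still to be reached. With two targets on record, a reader of the final report cannot tell whether the trial reached its planned size.

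Second, the allowance for attrition looks like the common slip of multiplying by one plus the loss rate instead of dividing by one minus it. If so, the larger target also falls short of the number on which the power statement rests. What is at stake is the accuracy of the stated 87% and, more practically, which sample size the trial is held to.

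**Working it through.** **Inputs.** From Power Analysis and Sample Size: 500 participants (250 per group), 87% power, significance level .05, attrition about 22%, enrolment 610, mean difference 1, SD 2.44. From Data Analysis, Aim 2: a two-tailed test. From Study Participants: 500 enrolled.

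**Step 1. Reproduce the 610.** 500 × (1 + 0.22) = 610 exactly, so the origin of the number is clear.

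**Step 2. Correct inflation.** To keep n after a proportion d is lost, enrol n/(1 − d): 500/(1 − 0.22) = 500/0.78 = 641.03, so 642 (321 per group). That is 642 − 610 = 32 more than stated.

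**Step 3. What each stated target leaves.**

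| Enrolled | Calculation | Left after 22% loss |
|---|---|---|
| 610 | 610 × 0.78 = 475.8 | about 476 (238 per group) |
| 500 | 500 × 0.78 | 390 (195 per group) |

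The approximate sign before 22% does not rescue 610. It leaves 500 only if attrition is 110/610 = 18.0%. At 20% it leaves 488.

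**Step 4. Try to reproduce the 87%.** A simple two-sample comparison with difference 1, SD 2.44 and 250 per group has standard error 2.44 × √(2/250) = 0.218. The ratio is 1/0.218 = 4.58, and the power is Φ(4.58 − 1.96) = 99.6%. Adding six measurements with within-person correlation 0.1 takes it above 99.9%. Variants with a random slope range from about 7% to 100%, depending on the time scale and the contrast tested, which are not printed. None of the variants came within 2 points of 87%. The consequence for power can therefore only be scaled from the stated figure.

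**Step 5. Scale from the stated 87%.** The implied noncentrality at 500 is 1.960 + 1.126 = 3.086. At N it is 3.086 × √(N/500), and power is Φ(that value − 1.960).

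| N giving data | Noncentrality | Power |
|---|---|---|
| 500 | 3.086 | 87.0% |
| 476 | 3.011 | 85.3% |
| 390 | 2.726 | 77.8% |
| 610 (no loss) | 3.409 | 92.6% |

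The rows for 476 and 390 treat every dropout as contributing nothing. Used one-sided, the same scaling gives 85.5% and 78.9%, so sidedness hardly matters.

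**The case against.** The defence has several fair points.

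- **The loss from the inflation slip is small.** It is 87.0 − 85.3 = 1.7 points, and that is a worst case. The planned generalised linear mixed model uses the visits that participants complete before leaving. On the scaled figures, true power with 610 enrolled lies between about 85% and about 93%. This stands. A reader might infer that the trial cannot deliver roughly its stated power; with 610 enrolled the documents do not support that.
- **The Abstract can be read differently.** It speaks of collecting data from 500, not of enrolling 500, and could mean 500 with complete data. This stands in part, though collection is said to begin at baseline, before any attrition. The direct conflict is between Study Participants and the power section. The Abstract and the n=25 figure are only supporting evidence.
- **The scaled powers rest on a figure that could not be re-derived.** This stands and limits how precisely the consequence can be stated. It does not affect Steps 1 to 3, which use only printed numbers.

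A reader might also infer that the 22% contradicts the Aim 1 power assumptions, where "The anticipated proportions missing at each measurement time are 0.00, 0.08, 0.16, 0.24, 0.32, and 0.40", and that power should be recomputed with 40% lost. The documents do not support this. Those are missing proportions at each visit, and they average 1.20/6 = 20% over the six time points, close to 22%. Under the End Points section a participant also leaves when chemotherapy ends, so a missing T6 value need not be attrition. The 87% concerns a difference in group means over 6 to 30 measurements, not a contrast at T6, so it cannot be scaled by the T6 proportion alone.

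**Conclusion.** Both faults hold on the printed numbers. The article commits to enrolling 500 in one section and 610 in another, without saying whether 500 is enrolled or evaluable. The 610 is also the wrong inflation: at 22% attrition it leaves about 476, and 642 would be needed to keep 500.

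The size of the consequence depends on which target governs. With 610 enrolled, power is at worst about 85% against the stated 87%, which is minor. With 500 enrolled, about 390 remain and power is at worst about 78%, which is material. Both figures assume that the stated 87% is right, that attrition is 22%, and that dropouts give no data. The main reason to act is the conflict over the target; the loss of power through the 610 error is secondary.

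**What to change.** State one enrolment number throughout, and say whether 500 means enrolled or evaluable. Then take one of these routes:

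- **610 is the target.** Replace 500 (250 per group) in the Aim 2 power statement by about 476 evaluable (238 per group) and 87% by about 85%, preferably re-run in PASS 20 with the original settings. Correct the 500 in Study Participants and the Abstract, and the n=25 that follows from it. Cost: wording and a slightly lower stated power, with no extra participants.
- **500 is the target.** Remove 610 and state about 390 evaluable and about 78% power, again preferably re-run. Cost: a visibly lower stated power, with no extra participants.
- **500 evaluable is meant.** The number that keeps 500 at 22% attrition is 642. Cost: 32 participants more than 610.

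Whichever route is chosen, printing the measurement schedule, time scale and PASS procedure behind the 87% would let a reader check it.
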